#### Secondary outcomes

Overall survival, defined as time from randomisation to death (any cause), evaluated at two and five yearsLocal, regional and extra-hepatic/systemic recurrence of disease at two years post randomisation (as defined above)DFS (measured from end of intervention) at two years post randomisation (as defined above)Use of subsequent therapies within two years post randomisation after treatment failure, for example, use of additional radiofrequency ablation or surgery for recurrence in either armHealth-related quality of life (EQ-5D, EORTC QLQ-C30, EORTC LMC21) [37–39] at baseline, and 3, 6, 12, 18 and 24 months post randomisationComplications during treatmentPost-treatment complications using Clavien-Dindo classification system [40, 41]Length of intensive therapy unit (ITU) and inpatient stay (length of hospital related to treatment or treatment-related complications) at 30 days and 3 months after completion of treatment

Outcomes related to health economics and qualitative research are reported under the health economics section and qualitative research.

### Trial schema

The trial schema is shown in Fig. 1.

**Fig. 1 Fig1:**
[figure not shown]
Trial schema. The figure shows the pathway that participants who are potentially eligible for the trial follow

### Data analysis

#### Statistical analysis

Analysis and reporting will be in line with CONSORT guidelines. Analyses will be carried out on both an intention-to-treat (ITT) basis and per-protocol (PP) basis. Non-inferiority hypotheses will be tested at the one-sided 2.5% level of significance. Superiority hypotheses will be tested at the two-sided 5% level of significance. 95% confidence intervals for parameter estimates will also be reported.

The primary analysis will assess the difference in DFS. The non-inferiority hypothesis will be tested using an appropriate survival model to incorporate random effects with respect to research site and including adjustment for the stratification factors. The specific survival model that is most ‘appropriate’ cannot be determined a priori; for example, the Cox proportional hazards model will be considered but will not be used if the proportional hazards assumption is violated. Patients for whom an event is not reported during their trial follow-up will be censored at the last date that they were known to not have had an event.

Differences in rates such as complication rates and recurrence rates will be analysed using multi-level logistic regression incorporating random effects with respect to research site and will include adjustment for the stratification factors.

Subgroup analysis based on the type of surgery (open or laparoscopic liver resection) and type of ablation (RFA or MWA) will be performed. If there are truly substantial differences in efficacy between types of treatment within an arm, then these subgroup analyses, while likely having limited precision, will give an unbiased indication of the magnitude and direction of the differences. This will allow us to explore how the treatment effect partitions into these more precise components, which will allow us to assess the validity of assumption that there is no substantial difference in efficacy between open and laparoscopic surgery, and there is no substantial difference between RFA and MWA. This will also allow us to perform sensitivity analyses using imputation methods to assess the impact of changing the proportion of each type of treatment performed within arm on the primary treatment effect estimate. This will facilitate the generalisability of our inferences to wider practice and to potential changes in the uptake of each type of treatment over time.

Continuous measures such as length of ITU and hospital stay will be analysed using multi-level normal-errors regression incorporating random effects with respect to research site and including adjustment for the stratification factors. In the case of deviation from the Normality assumptions, the appropriately transformed variable will be analysed.

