### When can one consider ablation to be equivalent to liver resection in terms of long-term results?

Liver resection for CLM is a major surgical procedure and carries a postoperative mortality of approximately 3–4% and a complication rate of ~ 40% [31]. Because of the effects of major surgery and the associated pain, the patients take about 2–3 months to recover from surgery and the quality of life is only 0.65 on a scale of 0 to 1 (1 indicating perfect health) even six months after liver resection [25]. As the patient group identified for this trial are those considered high-risk in terms of age, co-morbidity and the extent of liver resection required, the mortality, morbidity and length of hospital stay are likely to be considerably higher than the average and the health-related quality of life and recovery period significantly greater.

In contrast, the ablative methods have fewer complications (6%) [26] and the quality of life is 0.74 (on a scale of 0 to 1) by three months [25]. An informal discussion with patient representatives from Bowel Cancer UK suggested they were willing to trade-off 3–6 months (average 4 months) of their long-term survival in return for a less-invasive procedure with significantly lower complication rates compared to surgery. So, on average, the long-term results of ablation and surgery can be considered equivalent if the difference in long-term survival between the modalities is < 4 months. Clearly, if ablation results in similar or better survival, ablation is the better option since it is less invasive and results in better quality of life in the short-term.

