### Sample size calculations

A total of 330 patients are required to demonstrate non-inferiority (non-inferiority margin of four months) of thermal ablation with respect to resection in terms of DFS with 80% power at the 2.5% one-sided level of significance, allowing for a four-year accrual period, two-year follow-up, and assuming 14 months DFS in the resection arm and allowing for a 5% drop-out rate.

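### The four-month DFS margin is given no summary measure or hazard ratio, and the primary model is left to depend on a proportional-hazards check, so the trial's own data can settle what four months means

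*Protocol article*

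**What the plan says.** Under Sample size calculations, the protocol article gives a "non-inferiority margin of four months" on DFS, "assuming 14 months DFS in the resection arm". It does not say whether either figure is a median, a mean or a restricted mean, and it gives no hazard ratio. The test is "at the 2.5% one-sided level of significance", with 80% power.

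Under Statistical analysis, the primary analysis is of the difference in DFS, through an appropriate survival model with random site effects and adjustment for the stratification factors. The section adds that the specific model cannot be settled beforehand. Its one example is that "the Cox proportional hazards model will be considered but will not be used if the proportional hazards assumption is violated". No diagnostic, threshold or fallback model is named, and four months is not translated into any model's parameter.

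Under Endpoints, the primary endpoint is labelled DFS at two years but defined as a time to event, with failed treatments given an event time of 0.

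The four months come from the Background, where patient representatives put a length on the long-term survival they would give up for a less invasive procedure. The long-term results "can be considered equivalent if the difference in long-term survival between the modalities is" under four months.

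**The concern.** A non-inferiority test controls its error rate only if one effect measure and one margin on that measure are fixed before outcomes by arm are seen. Here the only model named yields a hazard ratio, for which no margin is printed, and it is discarded if a property of the outcome data fails. The replacement would bring its own effect measure, and four months on that measure can be a much looser or tighter limit.

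The trigger could well occur. The article sets treatment failures to time 0, expects early mortality after resection in this group to exceed the general 3–4%, and describes high local recurrence after ablation. Each could make the hazard ratio change over time. At stake is whether the same data set passes or fails.

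**Working it through.** **Inputs.** Resection DFS 14 months, margin 4 months, one-sided 2.5%, 80% power, "allowing for a four-year accrual period, two-year follow-up", 5% drop-out (all from Sample size calculations); 1:1 allocation (eligibility section). Assumed: exponential DFS, uniform accrual and, unless noted, 14 months as a median.

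**1. Reproducing the 330.**
- HR at the margin: 14/(14 − 4) = 1.40.
- Events (Schoenfeld): 4 × (1.960 + 0.842)² / (ln 1.40)² = 277.3.
- λ = ln 2/14 = 0.0495 per month. Event probability with 48 months of accrual and at least 24 months of follow-up: 1 − [e^(−24λ) − e^(−72λ)]/(48λ) = 0.8837.
- N = 277.3/0.8837 = 313.8; divided by 0.95, 330.3.

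Other readings, all with HR 1.40:
- Freedman's formula: 336.6.
- 14 months as a mean, staggered follow-up: 307.5.
- 14 months as a mean, every patient stopped at 24 months, event rate averaged over the arms: 337.6.
- Medians, every patient stopped at 24 months: 419.9.

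A few fall within 3% of 330. Only medians of 14 and 10 with follow-up to 24 months after the last patient match to the patient.

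**2. What four months means on each scale** (control median 14).

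| Scale | Calculation | Limit as HR |
|---|---|---|
| Medians | 14/10 | 1.40 |
| Full mean | 14/ln 2 = 20.2; 20.2/(20.2 − 4) | 1.25 |
| Restricted mean to 24 months | (1 − e^(−24λ))/λ = 14.04; HR that lowers it to 10.04 | 1.76 (ablation median 7.9 months) |

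Conversely, HR 1.40 gives restricted means of 14.04 and 11.69, a difference of 2.35 months. If four months is held fixed on the median scale, the HR limit also moves with the control median: 10/6 = 1.67 at a median of 10 months and 20/16 = 1.25 at 20.

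**3. Pass rate at HR 1.40.** Evaluable patients per arm: 330 × 0.95/2 = 156.75. The standard error of the 24-month restricted-mean difference is 0.959 months.
- Restricted mean against four months, used outright: Φ((4 − 2.35)/0.959 − 1.96) = 0.41.
- Restricted mean against 2.35 months: Φ(−1.96) = 0.025.
- Cox against 1.40 unless a 5% proportional-hazards test rejects, then restricted mean against four months: roughly 0.95 × 2.5% + 0.05 × 40.6% = 4.4%. Simulation (1,500 runs, 314 patients) gives 3.8% with every patient followed for 24 months and 5.5% with staggered follow-up.

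**4. Disagreement between the two tests** (same simulation, 24 months of follow-up each). At a true HR of 1.2, Cox against 1.40 passes in 22% of trials and the restricted mean against four months in 83%; they disagree in 61%. In one simulated data set with a proportional-hazards z of −2.56, Cox gives HR 1.11 (95% CI 0.85 to 1.44), which fails 1.40. The restricted-mean difference is −1.56 months (−3.51 to 0.39), which passes −4.

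**5. How often the switch might occur.** The article gives no failure rate. If 10% of ablation patients alone fail at time 0 and the rest have HR 1.0, a 5% proportional-hazards test rejects in 38% of trials; with 5% to 20% failing it rejects in 15% to 90%.

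**The case against.** Three points can be made for the plan.

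First, this is a journal article. The hazard-ratio equivalent of the margin, the diagnostic and the fallback are commonly left to a fuller protocol or SAP, which may settle them before data are seen. That stands for those details. It does not dispose of the point, because the article does more than defer: it says that the model cannot be fixed in advance and ties the choice to an assumption that can only be checked on outcomes by arm. When, and by whom, the check would be made is not stated, so it cannot be said that the choice will be made unblinded, only that the text allows it.

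Second, a reader might infer that the margin has no scale at all, or that the sample size is wrong. Neither is supported. The margin has a unit, months of DFS, and HR 1.40 can be recovered from the 330. What is missing is the summary measure and the model parameter.

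Third, a reader might take 41% as the plan's error rate. It is not. The article never mentions a restricted mean, and a treatment at HR 1.40 loses only 2.35 restricted-mean months, so on that scale it truly lies within four months. The rule as described, with this assumed replacement, gives about 4–5%.

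A reader might also infer that the article claims survival equivalence from DFS alone, or that overall survival needs its own margin. The article defines equivalence by long-term survival but nowhere says that DFS non-inferiority would establish it. Overall survival is collected to five years, and a secondary endpoint without a margin is normal.

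**Conclusion.** The point holds. The plan fixes neither the primary effect measure nor what four months means on it, and makes the one named model conditional on the outcome data. Plausible readings of the margin run from HR 1.25 to 1.76, while the sample size implies an unstated 1.40. Under proportional hazards, the modelled switch raises the pass rate at HR 1.40 from 2.5% to about 4–5%. That inflation is modest, but disagreement on individual data sets is not.

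These sizes rest on exponential DFS, a control median of 14 months, a 5% proportional-hazards test and the restricted mean as an example of a replacement. Another replacement would give other figures. The failure rates at time 0 are assumed.

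A narrower consequence follows from the margin's origin. It was elicited as a trade in long-term survival and is applied to DFS, so a positive result supports non-inferiority in DFS and no more.

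**What to change.** Before any unblinded outcome data are seen, name one primary effect measure, one model and the margin on that scale, to be used whatever the proportional-hazards check shows. Either choice below is defensible, with the other prespecified as supportive and not as a replacement:

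- **Cox hazard ratio**, with site effect and stratification factors: non-inferior if the upper 95% limit is below 1.40. This agrees with the 330 patients if follow-up runs to 24 months after the last patient.
- **24-month restricted mean DFS**, against its matching margin of about 2.3 months, not four.

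State that the 14 and 10 months are medians, if that was the intention. Word the primary conclusion as non-inferiority in DFS, and report overall survival with its 95% CI beside it.

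The cost is wording in the protocol and SAP. The Cox choice needs no change in N, but under non-proportional hazards its hazard ratio is an average effect, which the supportive restricted mean covers. The restricted-mean choice costs power: in the simulation at HR 1.0 it passes in about 68% of trials, against about 80% for Cox with staggered follow-up (71% if every patient stops at 24 months). Choosing it would mean revisiting N.

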**Methods:**

*Design and setting:* This is a multicentre, open, randomised controlled non-inferiority trial design with internal pilot and will be performed in tertiary liver centres in UK and The Netherlands.

*Participants:* Eligible patients will be those with colorectal liver metastases at high surgical risk because of their age, co-morbidities or tumour burden and who would be suitable for liver resection or thermal ablation.

*Intervention:* Thermal ablation as per local policy.

*Control:* Surgical liver resection performed as per centre protocol.

*Co-interventions:* Further chemotherapy will be offered to patients as per current practice.

*Outcomes*

Pilot study: Same as main study and in addition patients and clinicians’ acceptability of the trial to assist in optimisation of recruitment.

Primary outcome: Disease-free survival (DFS) at two years post randomisation.

Secondary outcomes: Overall survival, timing and site of recurrence, additional therapy after treatment failure, quality of life, complications, length of hospital stay, costs, trial acceptability, DFS measured from end of intervention.

*Follow-up:* 24 months from randomisation; five-year follow-up for overall survival.

*Sample size:* 330 patients to demonstrate non-inferiority of thermal ablation.

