### Post-treatment care

Participants will be reviewed in clinic at 3, 6, 12, 18 and 24 months post randomisation. Follow-up imaging investigations (CT scan chest, abdomen and pelvis minimum) and tumour markers will be performed following completion of successful treatment of the index disease until disease recurrence.

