### Endpoints

#### Primary endpoint

DFS at two years post randomisation.

DFS is defined as the time from randomisation to the first event, which is defined as any of the following:Local, regional or extra hepatic/systemic recurrence of diseaseDeath (any cause)

The time-to-event for patients whose treatment fails will be set equal to 0. If, according to post-intervention assessment, the index disease is deemed to have not been successfully removed/eradicated, then the treatment will be classed as having ‘failed’. Local recurrence is defined as the detection of disease at the treatment site after successful trial intervention. Regional recurrence is defined as detection of disease in the liver—not related to the treatment site—after successful trial intervention.

Extra-hepatic/systemic recurrence is defined as detection of new disease at any site other than the liver after successful trial intervention. ‘New disease’ refers to any extra-hepatic/systemic disease which was not already detected before commencement of trial treatment. The date of recurrence is defined as the date of the relevant assessment which detected the recurrence.

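### Site-specific recurrence at two years is assigned to logistic regression, but follow-up imaging ends at first recurrence, failed treatments cannot count, and timing is a listed outcome

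*Protocol article*

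**What the plan says.** All references are to the protocol article.

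- **Method** (Statistical analysis): "Differences in rates such as complication rates and recurrence rates will be analysed using multi-level logistic regression", with random effects for site and adjustment for the stratification factors.
- **Outcome** (Secondary outcomes): local, regional and extra-hepatic recurrence, each at two years after randomisation. The abstract's outcome list gives "Overall survival, timing and site of recurrence", so timing is an outcome too.
- **Definition** (Primary endpoint): "Local recurrence is defined as the detection of disease at the treatment site after successful trial intervention". This is not limited to the first recurrence. A treatment that does not clear the index disease is a failure and has its DFS time set to 0.
- **Imaging** (Post-treatment care): follow-up CT and tumour markers "will be performed following completion of successful treatment of the index disease until disease recurrence". Clinic review is scheduled to 24 months.
- **Censoring** (Statistical analysis): "Patients for whom an event is not reported during their trial follow-up will be censored at the last date" they were known to be event-free. This stands in the paragraph on the DFS survival model; the recurrence analysis has no counterpart.
- **Populations** (Statistical analysis): "Analyses will be carried out on both an intention-to-treat (ITT) basis and per-protocol (PP) basis".

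**The concern.** High local recurrence is the article's main reservation about ablation (Effectiveness of ablation methods; Potential concerns about thermal ablation compared with surgery). The arm comparison of local recurrence will therefore be read closely beside DFS, although it is secondary.

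The analysis needs a two-year status for every patient, and the follow-up does not deliver one. A patient who first recurs in the lung leaves scheduled imaging, and later disease at the treatment site is then found only if care outside the schedule finds it. A patient who dies early or is lost has no two-year status. A patient whose treatment fails has the poorest local result but cannot, by definition, have a local recurrence. A binary model has no place for these differences, nor for the timing of recurrence.

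These events need not be balanced. The article gives 3–4% postoperative mortality after resection, expects it to be considerably higher in this population, and describes practically no short-term mortality after ablation. Failure to clear the index disease may also differ by arm.

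**Working it through.** **1. The plan's own figure.** The article gives no number for the recurrence analysis, so the check starts from the sample size, to confirm how the 14-month DFS is meant. The inputs are "non-inferiority margin of four months" and "with 80% power at the 2.5% one-sided level of significance, allowing for a four-year accrual period, two-year follow-up", with 14 months in the resection arm and 5% drop-out.

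- Hazard ratio at the margin: 14/10 = 1.4.
- Events: 4 × (1.960 + 0.842)² / (ln 1.4)² = 278 (rounded up).
- Event probability, exponential with median 14 months, uniform 48-month accrual, follow-up from 24 to 72 months: 0.884.
- N = 278/0.884 = 315; 315/0.95 = 332, against the stated 330.

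The figure reproduces, so 14 months can be read as an exponential median: λ = ln 2/14 = 0.0495 per month. The follow-up pattern is one reading of the sample-size statement and is not at issue here.

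**2. How many patients have a first event by 24 months.** 1 − exp(−24 × 0.0495) = 0.695. About 70% leave the state in which a first local recurrence can be observed.

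**3. Illustrations.** Let L, O and D be the monthly hazards of local recurrence, recurrence elsewhere and death. Let c = −ln(0.95)/24 be the hazard of loss, and T = 24.

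- *Continued*: local recurrence before death had imaging continued = L/(L+D) × [1 − exp(−(L+D)T)].
- *Recorded*: local recurrence when imaging stops at first recurrence and anyone unobserved is coded no = L/(L+O+D+c) × [1 − exp(−(L+O+D+c)T)].

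All hazard splits are assumptions. The 13% and 46% come from a series quoted in the article as recurrence, not labelled local, first-site or two-year; they serve only as inputs.

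| Scenario (surgery; ablation) | Continued | OR | Recorded | OR |
|---|---|---|---|---|
| A: L/O/D = 13/72/15%; 46/49/5% of λ | 13.1% v 41.0% | 4.59 | 8.9% v 31.3% | 4.70 |
| B: 30/50/20%; 30/30/5% of λ | 26.9% v 29.2% | 1.12 | 20.4% v 24.3% | 1.25 |
| C: 30/50/20%; 30/50/5% of λ | 26.9% v 29.2% | 1.12 | 20.4% v 22.0% | 1.10 |
| D: 24-month net risks 13/50/10%; 46/50/4% | 12.4% v 45.2% | 5.84 | 8.8% v 33.1% | 5.11 |

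In B the local hazards are equal, so the cause-specific hazard ratio is 1.00 by construction, yet the binary analysis gives 1.25. In A and C the odds ratio barely moves. In D it falls. Neither direction nor size is determined.

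**4. Dependence on coding.** Under the coding above, the recorded figure falls short of the continued one by 17% (B, ablation: 1 − 0.243/0.292) to 33% (A, surgery: 1 − 0.0885/0.1314). If patients who die, are lost or recur elsewhere first are dropped instead, scenario A reads 23.4% v 52.0%, which is too high in both arms. The article does not say which coding applies.

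**5. Loss alone.** In scenario A, 5% loss moves the ablation figure only from 32.0% to 31.3%.

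**6. Treatment failures.** Let f be the proportion failing and p the first-site local recurrence among the rest. Local recurrence over all randomised is (1 − f)p, and local failure is f + (1 − f)p, so the two differ by f. With p = 32.0% (scenario A, ablation) and f = 10% (assumed): 0.9 × 0.320 = 28.8%, against 38.8%.

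**The case against.** The case for leaving the plan alone has real force.

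- **A fixed-horizon proportion is legitimate.** With near-complete follow-up to 24 months and death as a non-event, the two-year proportion is the cumulative incidence. This stands: death alone is a matter of estimand, and step 5 shows that 5% loss matters little. It does not answer the end of scheduled imaging or the exclusion of failures.
- **Coding of unobserved patients is commonly left to an analysis plan, which is not shown.** This stands, so no direction of bias can be asserted. The mismatch between method, imaging and definition is in the article itself.
- **Later local recurrence may still come to light**, since clinic review continues, recurrent disease goes to multidisciplinary review, and subsequent therapy is recorded to two years. This is partly right, but it is not systematic ascertainment.
- **Failures count in full in DFS.** They do, but a reader comparing local control by arm will not see them in local recurrence.

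A reader might infer that about a third of local recurrence is hidden and that a competing-risks analysis would recover it. Setting first-site incidence after surgery at 13% gives a local hazard of 0.13 × 0.0495/0.695 = 0.00926 per month. Then 1 − exp(−24 × 0.00926) = 20%. Tripling that hazard for ablation (assumed) gives 33% against 49%. The document does not support that inference. The 20% and 49% are risks with every competing event removed, death included, and the 13% is not labelled local. A cumulative-incidence estimator with those competing events targets the 13% and 33%.

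**Conclusion.** The point holds as a mismatch between the stated analysis and the data that the follow-up will yield. A two-year yes/no for any local recurrence is not systematically ascertained after recurrence elsewhere, makes no use of censoring or timing, and excludes treatment failures. Because early death, and possibly failure, may differ by arm, the odds ratio can reflect competing events as well as local control.

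The size is uncertain: an apparent odds ratio of 1.25 under equal local hazards in one illustration, almost no shift in two others. These figures rest on constant hazards, assumed splits, complete non-ascertainment after first recurrence, and coding of the unobserved as no. It would go beyond the document to say that local recurrence is understated by a known amount or that the arm comparison is biased in a known direction.

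The outcome is secondary. Primary DFS is a composite with its own survival model and is unaffected. The change is worth making but is not critical to the main conclusion.

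**What to change.** 1. Define the outcome as **site of first recurrence** (local, regional, extra-hepatic), which the imaging schedule can support as it stands.
2. Report **cumulative incidence by arm** (Aalen-Johansen), with death and first recurrence elsewhere as competing events and censoring at last disease assessment. State how treatment failures enter, so that the denominator remains all randomised patients.
3. Compare arms with **cause-specific Cox models** adjusted for the minimisation factors and site, with Fine-Gray as a supplement. The cause-specific model is the one that returns a ratio of 1.00 in scenario B; cumulative incidence there is still 20.9% v 24.8%, so both should be shown.
4. Add **local failure**, meaning treatment failure or local recurrence, analysed by intention to treat.
5. Keep multi-level logistic regression for complications.

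The cost is wording and a little more programming. DFS already needs the recurrence and death dates, so no extra patients or scans are required. The downside is that local recurrence will mean first-site recurrence only. The revised analysis does not estimate the risk had imaging continued, and the report should say so.
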